#### Secondary goals

A set of experimental and diagnostic tools is combined to identify structural and biomechanical etiological factors in SIS patients, which will be related to clinical and functional status:

A. Presence and severity of pathologies in the subacromial space with MRI, e.g. (partial) cuff-ruptures, tendinosis, fibrosis or a subacromial inflammatory reaction, and assessment of cuff degradation status.

B. Acromial shape classification and 3D shape parameters of the humerus, scapula and subacromial space volume, using conventional radiographs and segmented MRI-arthrographies.

C. Quantification of cranialisation of the humerus with respect to the scapula at rest and during active arm abduction and adduction tasks with simultaneously acquired shoulder radiographs and Electromyography (EMG) recordings (see D).

D. Measurements of the activation of arm adductors during arm abduction tasks and assessment of the presence of arm adductor co-activation (Activation Ratio).

E. Analyses of 3D-kinematics (arm range of motion and scapulohumeral rhythm) of the affected SIS shoulder compared to the unaffected shoulder and eventual etiologic SIS subgroups, with the use of 3D motion registration.

F. Changes in reconstructed subacromial volume and acromiohumeral distance during arm abduction by combining the recorded 3D-kinematics with the MRI-segmented 3D bony shapes.

G. The effect of a subacromial infiltration of lidocaïne on arm range of motion, scapulohumeral and -thoracic rhythm with arm abduction, reconstructed subacromial volume and muscle activation patterns, including adductor co-activation.

H. Biomechanical analyses of structural or coordinative muscular imbalance by means of model simulation (Delft Shoulder and Elbow Model) with recorded 3D-kinematics as input.

I. Clinical phenotyping, using validated clinical scores and questionnaires.

J. Identification of alternative diagnoses that may cause complaints clinically diagnosed as SIS, using MRI and radiographs (e.g. acromioclavicular-osteoarthritis and subacromial osteophytes, calcifying tendinitis, SLAP lesion or coracoid impingement).

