#### 3D kinematics and changes in subacromial volume (E, F, G)

Range of Motion (RoM) and 3D motions of forearm, humerus and scapula with respect to the thorax will be recorded by means of an electromagnetic tracking system: 'Flock of Birds' (FoB, Ascension Technology Corp, Burlington, VT, USA) and custom made computer software (FOBVis, Clinical Graphics, Delft, the Netherlands). The FoB obtains 3D kinematical data using sensors on thorax, scapula, humerus, forearm and thorax. After palpatory identifying three dimensional positions of standard bony landmarks of the arm, shoulder and thorax with respect to the sensors for each patient, local bone coordinate systems are created, based on the subject's individual anatomy. The glenohumeral rotation centre is estimated from the position of five scapular bony landmarks using linear regression [61]. The RoM of the following movements is measured: anteflexion, retroflexion, abduction in frontal plane, internal rotation in 0 and 90 degrees of arm abduction and external rotation in 0 and 90° of arm abduction.

3D kinematics and MRI bony segmentation (3D shape parameters of scapula and humerus) will be combined in custom made computer software (Articulus, Clinical Graphics, Delft, the Netherlands) to reconstruct the subacromial space volume and AH during recorded humerus elevations, allowing dynamic measurements of patient-specific subacromial space characteristics [5,62,63]. Additionally, the effect of a subacromial lidocaïne injection on RoM, scapulohumeral rhythm, reconstructed AH and subacromial volume of the affected shoulder will be analyzed.

*Main kinematic outcome parameters*: Passive and active RoM during standardized arm motions (with and without subacromial anaesthetics) of both arms; Scapulohumeral rhythm of affected and healthy arm; Reconstructed changes in AH and subacromial volume during dynamic arm abduction (combining MRI-based shape parameters and 3D RoM measurements).

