#### Patient phenotyping (I)

The radiological and biomechanical outcome measures will be related to patients' clinical status or phenotype. We combine an overall general health outcome measure (i,e, SF36), a regional (e.g. shoulder) outcome measure, and a disease- or condition-specific measure for patient assessment [65].

- SF-36: Questionnaire to measure quality of life, based on physical function, illness, pain and mental health [66].

- Illness Perception Questionnaire (IPQ): measures perception and impact of Illness [67].

- The Disabilities of the Arm, Shoulder and Hand (DASH) score: to quantify impact and functional impairment of shoulder arm and hand function [68].

- Constant Shoulder Score (CS): used by physicians to quantify the severity of symptoms and functional impairment in affected shoulders, compared to the unaffected shoulder [69].

- Western Ontario Rotator Cuff index (WORC): a self-reported outcome measure for assessing shoulder problems as a consequence of rotator cuff disease [70].

- Visual Analogue Scale (VAS) for pain during daily life activities and in rest.

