**Figure 4 F4:**
[figure not shown]
**Schematic outline for relating outcome measures to pathophysiological mechanisms**. We expect to identify one or more of the hypothesized etiological mechanisms in each SIS patient. These mechanisms might be related to the reported variations in SIS symptoms, course, and treatment outcome. (MRI = Magnetic Resonance Imaging, X-ray & EMG task = radiographs during EMG recorded abduction and adduction tasks for measurements of acromiohumeral distance, and FoB = 3D kinematics with Flock of Birds system).

The following scenarios are considered:

1) Dynamically reduced subacromial space, due to (relative) cranial translation of the humerus.

Humerus cranialisation causing encroachment of subacromial tissues will be characterized by limited AH in resting state on standard radiographs, further decrease in AH during abduction tasks, and decreased reconstructed subacromial volume (MRI). In some patients, this cranialisation might be (partially) compensated by I) co-activation of arm adductor muscles, and/or II) altered kinematics of the humerus and the scapula (scapulohumoral rhythm). Nevertheless, instead of a compensation mechanism, altered scapulohumeral rhythm can also be a cause of SIS in some patients (e.g. decreased scapula lateral rotation during arm abduction, with consequent relative cranial translation of the humerus). Pain is suspected to be the main trigger for compensation mechanisms. Therefore, we expect that these compensation mechanisms will be less manifest during the second round of experiments, after a subacromial injection with lidocaine.

Particularly relevant positive outcome measures for this subgroup are: decreased AH, low AR (adductor co-activation), altered Principal Action for adductor muscles, decreased reconstructed subacromial volume during active abduction, degeneration of rotator cuff muscles and altered scapulohumeral rhythm.

2a) Statically reduced subacromial space, due to structural narrowing (classic etiology). The subacromial space can be narrowed as a consequence of structural anatomic variations, e.g. a hooked acromion impinging on the subacromial tissues. These potential causes will be investigated and quantified using shoulder radiographs and (segmented) MRI-arthrographies.

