#### Statistical analyses

Patient data, including patient characteristics, physical examination, interview, radiological findings, questionnaires, psychological scores, biomechanical measurements and MRI findings will be entered in a database.

With regards to presence of cranial translation of the humerus as detected on radiographs during rest and abduction and adduction tasks, statistical analysis will be performed by a means of repeated measures ANOVA, with the measure of co-contraction controlled as a confounding factor.

For the isometric Principal Action EMG measurements, data are tested by means of a General Linear Model analysis for repeated measures, controlling for factors Muscle, subacromial anaesthetics, sAH and VAS for pain.

RoM in standardized motions will be analyzed with a General Linear Model analysis for repeated measures, controlling for factors VAS pain, subacromial anaesthetic, dAH and sAH. dAH obtained from 3D-kinematics will be analyzed equally.

Additionally, we will use students' unpaired t-tests to compare continuous variables (e.g. patient characteristics, clinical scores, RoM, dAH) between defined pathologic subgroups.

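### The lidocaine models adjust for variables that lidocaine is expected to change (VAS pain, dAH), so with post-injection values the anaesthetic term is not the total effect Goal G asks for

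*Protocol article*

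**What the plan says.** Goal G, under Secondary goals, is "The effect of a subacromial infiltration of lidocaïne on arm range of motion, scapulohumeral and -thoracic rhythm with arm abduction, reconstructed subacromial volume", and it goes on to name muscle activation patterns. The section on 3D kinematics and changes in subacromial volume adds reconstructed acromiohumeral distance (AH) to the lidocaine outcomes. It says that software combines the recorded motions with the MRI bone shapes "to reconstruct the subacromial space volume and AH during recorded humerus elevations". The section on EMG muscle activation patterns states a second hypothesis: after the injection, activation moves toward normal.

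The expected route is given in scenario 1 of the section relating outcome measures to mechanisms: "Pain is suspected to be the main trigger for compensation mechanisms". Compensation is therefore expected to be weaker in the second round of measurements.

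Statistical analyses then specifies:

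- Principal Action EMG: a repeated-measures general linear model "controlling for factors Muscle, subacromial anaesthetics, sAH and VAS for pain".
- RoM, and then dAH: the same type of model, "controlling for factors VAS pain, subacromial anaesthetic, dAH and sAH. dAH obtained from 3D-kinematics will be analyzed equally".

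The only pain scale described, under Patient phenotyping, is a "Visual Analogue Scale (VAS) for pain during daily life activities and in rest". No repeat after the injection is mentioned. The abbreviations dAH and sAH are not defined. From context I take dAH to be the AH reconstructed during motion and sAH to be a static AH.

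**The concern.** A model that contains both the anaesthetic and a variable the anaesthetic changes splits the effect. The anaesthetic coefficient keeps only what does not pass through that variable. On the protocol's own theory VAS pain lies on the path from lidocaine to activation and motion. dAH is itself a lidocaine outcome, computed from the same recorded motions as RoM.

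Goal G and the second hypothesis ask whether lidocaine changes these outcomes, which is a question about the total effect. A model that holds pain or dAH fixed at post-injection values answers a different question. The more nearly right the pain theory is, the smaller its answer becomes. A null anaesthetic term could then be read as evidence against the mechanism when it is what that mechanism predicts. This matters for interpretation because scenarios 1 and 2a both use the expected weakening of compensation after lidocaine.

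**Working it through.** The plan gives no figure for this point, so there is nothing to reproduce. The check is an illustration, and every numerical input to it is an assumption.

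**Inputs (assumed):** 100 patients measured before and after injection; true total effect on RoM 10 degrees; VAS before injection mean 5 (SD 2); VAS change mean −3 (SD 1.5); residual SD 6 degrees per measurement; a share *s* of the effect acting through pain.

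**Model.** With b = −10*s*/3 degrees per VAS point and d = 10(1 − *s*), the within-patient change is

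ΔRoM = d + b·ΔVAS + (e₁ − e₀), where SD(e₁ − e₀) = 6√2 = 8.49.

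**Total effect (no post-injection covariate).** The mean of ΔRoM is d + b(−3) = 10(1 − *s*) + 10*s* = 10 for every *s*.

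**Anaesthetic term with VAS change in the model.** This is the intercept at ΔVAS = 0, which is d = 10(1 − *s*). Its standard error is about 8.49·√(1/100 + 3²/(100 × 1.5²)) = 8.49·√0.05 = 1.90.

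**Results** (300 simulated studies per row; two-sided 5% test):

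| Share through pain | Unadjusted estimate | Adjusted, expected | Adjusted, simulated | Rejection rate, adjusted |
|---|---|---|---|---|
| 0% | 10.05 | 10.0 | 10.02 | 1.00 |
| 25% | 9.99 | 7.5 | 7.54 | 0.97 |
| 50% | 9.95 | 5.0 | 5.03 | 0.74 |
| 75% | 10.01 | 2.5 | 2.49 | 0.26 |
| 100% | 10.00 | 0.0 | −0.05 | 0.05 |

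The unadjusted contrast rejects in every simulated study. The adjusted rejection rates agree with the standard error above; at 50%, for example, 5.0/1.90 = 2.6, and Φ(2.6 − 1.96) is about 0.74.

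**Baseline VAS only.** With pre-injection VAS, centred at its mean, the estimate equals the unadjusted one in every row and the rejection rate is 1.00. The loss therefore comes entirely from post-injection values.

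**dAH in the RoM model.** No figure can be given, because nothing in the article fixes how dAH and RoM move together. Both are lidocaine outcomes taken from the same motions. If dAH lies on the path to RoM, the algebra above applies with dAH in place of VAS. If the two are parallel consequences, the adjusted term is neither a total effect nor a clearly defined direct one. This limb does not depend on when VAS is taken.

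**dAH in its own model.** Read to the letter, regressing the change in dAH on itself gives slope 1 and intercept 0, so the anaesthetic term is exactly 0 whatever the truth.

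**The case against.** The strongest reply is about timing. The one VAS described covers daily life and rest, is listed with the phenotyping questionnaires, and has no stated repeat. A classical repeated-measures general linear model usually takes one covariate value per patient. On that reading the lidocaine contrast is intact. This stands, and it makes the VAS limb conditional. It does not reach the explicit adjustment of RoM for dAH.

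Second, VAS has a legitimate place in some model. The EMG section says the before/after measurements serve to relate pain during abduction to co-activation and kinematics, and the covariate lists, which include the anaesthetic and the muscle, may be loose lists of model terms. This also stands, but it is a reason for a separate analysis of pain. The total effect of lidocaine still needs a model of its own, and the article states none.

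A reader might draw four stronger conclusions that the article does not support:

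- *The plan removes the lidocaine effect.* That needs post-injection values and full mediation. The article calls pain the suspected main trigger, not the only one, and partial mediation attenuates the effect without abolishing it.
- *The dAH model is circular.* The sentence more probably means the same type of model with dAH as response and dropped from the covariates. It is a wording defect.
- *Every lidocaine model adjusts for dAH.* The EMG model does not, so the second hypothesis is touched only through VAS.
- *The pain aim cannot be tested.* A condensed article may leave a task-level pain score to the full protocol, and its silence does not show that none is recorded.

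**Conclusion.** The point holds in a conditional form. As written, the lidocaine models include covariates that the protocol itself expects lidocaine to change: VAS pain in the EMG and RoM models, and dAH in the RoM model. Where these carry post-injection values, the anaesthetic term falls short of the total effect by the share that acts through them. In the illustration that is a quarter, half, three quarters or all of the effect at the corresponding mediated shares. The loss through VAS is nil if VAS is a baseline value.

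The proportional loss follows from the linear model. The rejection rates also depend on the assumed sample, VAS change and residual SD. The timing of VAS and dAH in the models, and the meaning of dAH, are unstated, and I have assumed the latter from context. The consequence is confined to a secondary goal. Neither the primary classification goal nor the sample size calculation uses this coefficient.

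**What to change.** In Statistical analyses:

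1. Estimate the Goal G effect from a before/after repeated-measures contrast, with motion or muscle as a factor and only pre-injection covariates (baseline VAS, sAH), centred.
2. Remove dAH from the RoM model, and state that it is not a covariate in its own model.
3. Keep post-injection VAS out of all models for the lidocaine effect.
4. Report the relation of change in pain to change in activation or RoM as a separate analysis. It needs VAS marked at the task before and after injection; add this if the full protocol does not already record it.
5. Define dAH and sAH, and state when VAS and dAH are taken.

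The cost is a few sentences, one additional set of analyses and at most two VAS marks per patient in a session that already takes place. The VAS marks must be settled before the measurement sessions, since they cannot be recovered later; the rest can be settled before analysis.

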#### Sample size

A combination of techniques will be applied to classify SIS-patients into pathophysiologic subgroups, most of which are newly developed (section 2.3). The acromiohumeral distance (AH) is a recognized parameter related to rotator cuff disease and based on literature it has rather wide inter-individual variations. Therefore, sample size calculation will be based on this parameter.

In a study of Gruber et al., AH values of 9.4 (SD = 3.4) were observed in subjects without diagnosed cuff pathology. A subacromial space narrower than 6 mm on radiographs is considered pathologic and strongly indicative for supraspinatus tendon rupture [46].

The unpaired *t*-test was used to determine the sample size with a difference of AH of 3.4 mm between groups assumed as clinically relevant, comparing AH during abduction task radiographs in patients where humerus cranialisation plays a key-role compared to AH in other subgroups of SIS patients.

Based on the standardized difference: 3.4 mm/3.4 mm = 1.0, a required power of 80% and a p-value of 0.05 for significance, the Altman's Nomogram resulted in 30 shoulders/patients per group.

In our hypothesis, we defined 4 etiological mechanisms. Based on clinical experience and literature, we assume around 30% type III acromion responsible for complaints of SIS,[16] 20-30% of the SIS symptoms are caused by humerus cranialisation and pathologic motion patterns,[47] 15-20% by subacromial inflammatory processes without subacromial narrowing and 5-10% by other impinging structures than the acromion, leaving around 10-30% for a group in which SIS symptoms seem to be caused by two or more hypothesized etiologic mechanisms. With 30 patients needed in the humerus cranialisation subgroup (i.e. 30% of the patients), this leads to a total group size of 100 patients diagnosed with SIS based on patient history, physical examination, radiographs and MRI arthrography.

Additionally, we expect that around at least 25 patients will be diagnosed with another diagnosis than SIS after MRI-arthrography and radiographs [40,48]. These patients can not be included in the SISTIM study but selected patients will be analyzed separately in distinct research projects, if eligible (trial registry numbers:NTR1545 and NTR2282).

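### Student's two-sample t-test is fixed for comparing what the plan expects to be five unequal subgroups: false differences reach up to about 28% per variable, depending on the contrasts, and the pooled variance is fragile for the one small group

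*Protocol article*

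**What the plan says.** The last paragraph of Statistical analyses names the method for comparing subgroups: "we will use students' unpaired t-tests to compare continuous variables (e.g. patient characteristics, clinical scores, RoM, dAH) between defined pathologic subgroups". For these comparisons it gives no list of contrasts and no significance level. The only level in the article is in the sample size section, "a required power of 80% and a p-value of 0.05 for significance", without saying whether it is one- or two-sided.

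The number and size of the groups come from elsewhere in the Protocol article. The section on relating outcome measures to mechanisms sets out scenarios 1, 2a, 2b, 2c and a combination group. The sample size section assigns expected shares: about 30% type III acromion (2a), 20-30% humerus cranialisation (1), 15-20% inflammatory (2b), "5-10% by other impinging structures than the acromion" (2c), and the remainder, "leaving around 10-30% for a group in which SIS symptoms seem to be caused by two or more hypothesized etiologic mechanisms". The total is fixed by "this leads to a total group size of 100 patients diagnosed with SIS", so each percentage is also the expected number of patients.

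Two other places suggest fewer contrasts. The sample size section sets the cranialisation group against the other subgroups, and the Hypothesis section speaks of a dynamic and a static class.

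**The concern.** A t-test takes two groups at a time, and the plan describes five. Running it repeatedly at 0.05 raises the chance that some pair differs by luck, for every variable examined. The variables are numerous: the article lists six clinical instruments and seven range-of-motion movements, before any other measurement is counted.

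A second and separate weakness is that Student's version assumes equal variances. That assumption matters little when groups are of similar size. It matters a good deal when one group has 5-10 patients and another has 30.

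The Discussion plans to carry the classification into a later clinical trial. Subgroup differences that are only noise, or that the test hides, could therefore influence how that trial is built.

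**Working it through.** **Inputs.** Total 100; group sizes 30, 20-30, 15-20, 5-10 and 10-30 (Sample size). The shares are coherent: 100 - (30+20+15+5) = 30 and 100 - (30+30+20+10) = 10, which matches the 10-30% left for the combination group. Level 0.05 (Sample size), taken as two-sided. SD ratio between subgroups: not given, so a range of 0.5 to 2 is assumed.

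**The plan's own figure.** The article states no error rate for these comparisons. Its only t-test figure is "the Altman's Nomogram resulted in 30 shoulders/patients per group", for a standardized difference of 3.4/3.4 = 1.0. The usual formula gives n = 2 x (1.96 + 0.84)^2 / 1.0^2 = 15.7, so 16 per group (17 with the exact t distribution). The stated 30 is not reproduced; it would give about 97% power. That is a different question and does not bear on this point.

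**Multiplicity, equal variances.** Five groups make 5 x 4 / 2 = 10 pairs. The chance that at least one pair exceeds the two-sided 5% critical value is the chance that the studentized range of five means exceeds sqrt(2) x t(0.975; 95 df). Simulation (100,000 runs) with sizes such as 30/25/17/8/20 agrees.

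| Contrasts, per variable | Chance of at least one false difference |
|---|---|
| All 10 pairs of 5 groups | 28% |
| All 6 pairs of 4 groups | 20% |
| Cranialisation against each of the other 4 | about 16-17% |
| One two-group contrast (dynamic v static, or cranialisation v the rest pooled) | 5% |

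Ten independent tests would give 1 - 0.95^10 = 40%. Pairwise tests share groups and are correlated, so 28% is the right figure for all pairs. With 20 patients in every group it is still 28%, so the small group is not its cause.

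For scale, take 13 variables (six instruments with one score each, plus seven movements) and no true differences. The expected number showing at least one false difference is 13 x 0.28 = 3.6 for all pairs, 13 x 0.165 = 2.1 for one against each, and 13 x 0.05 = 0.65 for a single contrast.

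**Unequal variances, one pair.** Let n1 = 30 with SD 1 and n2 = 5 with SD 2. The pooled variance averages (29 x 1 + 4 x 4)/33 = 1.364, so the test takes the variance of the difference to be 1.364 x (1/30 + 1/5) = 0.318. The true value is 1/30 + 4/5 = 0.833. The t statistic is therefore spread about sqrt(0.833/0.318) = 1.62 times too widely. With SD 0.5 instead, the test uses (29 + 1)/33 x 0.2333 = 0.212 against a true 1/30 + 0.25/5 = 0.083, and is too cautious. Simulated type I error at nominal 5%:

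| Sizes | Small-group SD half | Equal | 1.5 times | Twice |
|---|---|---|---|---|
| 30 v 5, Student | 0.3% | 5% | 14% | 22% |
| 30 v 7, Student | 0.5% | 5% | 12.5% | 19% |
| 30 v 10, Student | 0.9% | 5% | 11% | 15% |
| 30 v 30, Student | 5.2% | 5.0% | 5.1% | 5.2% |
| 30 v 5 to 10, Welch | 5.0-5.3% | 5.2-5.8% | 5.2-5.6% | 5.1-5.6% |

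**The two issues are separate.** Replacing Student by Welch for all ten pairs leaves the rate per variable at about 28%. A method for several groups is needed as well.

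**What group 2c can support.** Even for a standardized difference of 1.0 with equal SDs, the t-test has 52% power at 30 v 5 and 76% at 30 v 10.

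**The case against.** The strongest reply is that the article nowhere says that all ten pairs will be tested. It names contrasts that need one test, or four. A reader might infer that the plan carries a 28% false-difference rate; the text does not support that as a statement of fact. The supportable range is 5% to 28%, depending on contrasts that remain unstated.

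A reader might also infer that several groups are tiny and that the t-test fails in them. Only 2c is expected at 5-10 patients; the combination group touches 10 only at its lower limit. No subgroup SDs are given, so the inflation is conditional, and in the opposite case the test is conservative. Subgroup 2c does collect mixed causes, which makes a larger spread plausible, but nothing in the article shows it.

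The study calls itself descriptive, its primary goal is to identify and classify mechanisms, and phenotyping is a secondary goal. These tests come after the repeated-measures analyses, as an addition. No confirmatory claim rests on them. Multiplicity rules and an overall test may also stand in an analysis plan that is not shown, so their absence from an article is no fault.

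All of this stands, and it limits the size of the point. It does not remove it. The article does not leave the method open: it names a two-sample, pooled-variance test for a structure that it describes itself as five groups of very different size.

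**Conclusion.** The point holds as a poorly chosen method, not as a missing detail. With two-sided 0.05 and equal variances, the chance of at least one false difference per variable is about 28% if all ten pairs are tested, about 16-17% if cranialisation is compared with each other group, and 5% only for a single two-group contrast.

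Independently of that, Student's test is miscalibrated for 2c against a group of 30 when the SDs differ: about 15-22% if the SD of 2c is twice as large and 0.3-0.9% if half as large. It is correct if they are equal, and Welch's test stays at about 5-6% throughout. The SD ratios are assumptions.

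Severity is minor to moderate, because these are secondary comparisons in a descriptive study.

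**What to change.** In Statistical analyses, replace the sentence on unpaired t-tests with wording along these lines: *Continuous variables will be compared across the etiological subgroups large enough to test by Welch's one-way ANOVA, followed by Games-Howell pairwise comparisons. Subgroup 2c will not enter these tests and will be described with means and confidence intervals. Any single two-group contrast, such as dynamic against static, will use Welch's t-test. All subgroup comparisons are exploratory.*

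The minimum size for entering the tests should be fixed before the analysis, because the combination group may be as small as 10. The intended contrasts should be listed in the same place.

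The cost is a change of wording. No patients, visits or measurements are added. The price is slightly less power for individual pairwise comparisons, and no formal test for 2c, where power would be low in any case.
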